#### Sphericity assessment

Atrial sphericity is automatically calculated using the left atrial sphericity predictor method.^20^ A best-fit sphere of the left atrium is calculated using the center of mass determined by the average radius of all left atrial wall points. The coefficient of variation of the sphere is then used to identify the best-fit sphere. The deviation of the segmented atrial body from the best-fit sphere is then calculated to quantify sphericity.

#### Additional postprocessing for assessment of iNav LGE imaging

An additional registration step is performed for alignment of the CE-MRA atrial segmentation and iNav LGE image. Pulmonary vein, left atrial appendage, and mitral valve clipping planes are registered and transformed from the dNav LGE image and overlaid to the iNav LGE image using the same image registration and transformation techniques described earlier. An LGE map can then be created and LGE and sphericity quantified as performed for dNav LGE imaging for comparison (Figure 3).

**Figure 3 fig3:**
[figure not shown]
Work flow for postprocessing of image-navigated late gadolinium enhancement (LGE) imaging. MRA = magnetic resonance angiography; R = registration.

#### Implantable loop recorder programming

All patients receive a Reveal LINQ (Medtronic) ILR device as per routine clinical care for detection of AF. Nominals are set to detect increased sensitivity of AF detection threshold, aggressive ectopy rejection, and storage of all AF/atrial tachycardia episodes to maximize AF detection. AF is detected following 2 minutes of ILR monitoring as per the Medtronic AF detection algorithm. Each episode will be reviewed by 2 independent experts prior to study/control group allocation. Daily remote data collection will occur as part of routine clinical care.

## Data analysis

Primary analysis will be performed following 12 months of continuous ILR monitoring with interim and delayed analyses performed at 6 months and 2 and 3 years, respectively. Descriptive statistics will be used to characterize the study population. Structural and electrocardiographic metrics will be summarized. Results will be reported as a comparison between the standard deviation and mean difference. If groups show a normal distribution, *t* test will be performed to assess for a significant difference between groups; otherwise, a Mann-Whitney *U* test will be used. The χ^2^ test will be used for categorical data. Any *P* value <.05 will be considered significant. For qualitative assessment of LGE, patients will be categorized as per our routine clinical practice using combined assessment of both LGE methods as none, mild, moderate, or severe LGE. Survival analysis will be performed using Kaplan-Meier curves with atrial fibrillation as the outcome measure. For qualitative assessment of atrial LGE, our open-source platform, CEMRGApp, will be used to create LGE scores. ROC analysis will be used to determine if there is a quantitative LGE cut-off with adequate specificity and sensitivity to detect atrial fibrillation during follow-up. To combine these variables into a single score, the use of logistic regression, shallow classifiers, atrial computational modeling, or combining variables using summated z-scores will be explored to improve the predictive value for AF.

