### Sample size justification

Previous data suggest that ILR monitoring will identify AF in 25% of ESUS patients with a CHA_2_DS_2_VaSc score of 3.^2^ We anticipate that our study population will have a 3:1 ratio of non-AF and AF patients. This ratio has subsequently been validated in the recent LOOP study.^28^

Pilot data analysis was performed using CEMRGapp, using the image intensity ratio to define atrial fibrosis at image intensity ratio >0.97.^29^ This analysis suggested a population mean difference of 6% in left atrial LGE burden between AF and non-AF patients, with standard deviations of 9% and 4% in the AF and non-AF group, respectively (Figure 2). For estimating the sample size required to detect a difference in LGE burden between stroke patients with and without AF, we allow for unequal variances and assume that cases (AF on ILR monitoring) represent 25% of the study population while controls (no AF on ILR monitoring) represent 75% of the study population. Group sample sizes of 21 and 63 would achieve 80.8% power to reject the null hypothesis of equal means when the population mean difference is μ1 − μ2 = 47.0 − 41.0 = 6.0, with standard deviations of 9.0 for group 1 and 4.0 for group 2, and with a significance level (alpha) of 0.05 using a 2-sided 2-sample unequal-variance *t* test.

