**Figure 2 fig2:**
[figure not shown]
Atrial cardiac magnetic resonance (CMR) pilot data in stroke and control patients. Illustration of atrial CMR findings in stroke (n = 8) and control patients (n = 8). **A:** Raw data and processed data appearances. **B:** Late gadolinium enhancement and sphericity quantification illustrating medians, interquartile ranges, and data ranges. IIR = image intensity ratio; LA = left atrium.

For estimating the sample size required to detect a difference in sphericity between stroke patients with and without AF, we again assume cases and controls represent 25% and 75% of the study population, respectively. Group sample sizes of 14 and 42 would achieve 82.5% power to reject the null hypothesis of equal means when the population mean difference is μ1 − μ2 = 80.0 − 77.0 = 3.0, with a standard deviation for both groups of 3.3 and with a significance level (alpha) of 0.05 using a 2-sided 2-sample equal-variance *t* test. Taking the larger of these estimates and allowing for 10% loss to follow-up indicates that a sample size of 92 patients is required for this study. With this sample size, assuming the 3:1 ratio of non-AF to AF individuals we would be able to estimate the area under the curve of a receiver operating characteristic (ROC) curve with 95% confidence interval width (upper-lower confidence limit) of between 0.21 and 0.28 for area-under-the-curve values between 0.85 and 0.65, respectively.

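### Left atrial LGE is sized on an unequal-variance t test, but the analysis rule chooses between an unspecified t test and Mann-Whitney by a normality check that does not address unequal spread

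*Protocol article*

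**What the plan says.** The Sample size justification section treats LGE (hypothesis 1 under Objectives) as a comparison of means with unequal spread. It says "we allow for unequal variances and assume that cases (AF on ILR monitoring) represent 25% of the study population". Its power statement is "Group sample sizes of 21 and 63 would achieve 80.8% power". The assumed means are 47.0 (AF) and 41.0 (non-AF), a difference of 6.0; the assumed SDs are 9.0 and 4.0 in the same order. The test is named as "using a 2-sided 2-sample unequal-variance" t test, at alpha 0.05. The smaller group, AF, thus has the larger SD.

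The same section sizes sphericity (hypothesis 2) separately: "Group sample sizes of 14 and 42 would achieve 82.5% power". There it assumes one SD of 3.3 for both groups and an equal-variance t test. LGE gives the larger number and therefore sets the total of 92.

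The Data analysis section does not return to these two tests. It has one rule for every structural and electrocardiographic metric: for groups that look normal, a t "test will be performed to assess for a significant difference between groups; otherwise, a Mann-Whitney" U test, with P below .05 counted as significant. It does not say whether the t test is pooled or unequal-variance, and it names no normality check.

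**The concern.** The rule switches on the shape of the distributions, whereas the difficulty the plan itself foresees is a difference in spread. When the smaller group is the more variable one, a pooled t test understates the standard error of the difference. Mann-Whitney is not protected either, because its null variance assumes identical distributions. Neither the switch nor the fallback guards against the situation on which the trial was sized.

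LGE is the first hypothesis of the principal research question. If the AF group is merely more variable, a significant result could appear with no difference in mean LGE burden. The stated alpha of 0.05 and power of 80.8% belong to a test that the analysis section does not name.

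**Working it through.** **Inputs, all from Sample size justification:** group sizes 21 (AF) and 63 (non-AF); SDs 9.0 and 4.0; mean difference 6.0; two-sided alpha 0.05; unequal-variance t test.

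**1. Reproduce the stated power.**
- SE = √(9²/21 + 4²/63) = √(3.857 + 0.254) = 2.028.
- Satterthwaite df = 4.111² / (3.857²/20 + 0.254²/62) = 22.7.
- Noncentrality = 6.0/2.028 = 2.959.
- Noncentral t power = 80.84%, against 80.8% stated.
- The plain normal approximation gives 84.1%, so the stated figure is specific to the Welch test.

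**2. What a pooled t test would do with equal means.**
- Pooled variance = (20×81 + 62×16)/82 = 31.85.
- Pooled SE = √(31.85 × (1/21 + 1/63)) = 1.422, against a true SE of 2.028.
- The test rejects when the difference exceeds about 1.99 × 1.422, which is 1.99 × 1.422/2.028 = 1.40 true standard errors. The large-sample two-sided error is 16.3%.

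**3. Simulation with normal data, equal means and SDs 9 and 4** (20,000 datasets). The two-step rows use Shapiro-Wilk at 0.05 in each group. That check is an assumption, since the document names none. The second column splits the full 92 patients 1:3.

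| Test | 21 / 63 | 23 / 69 |
|---|---|---|
| Pooled t | 16.8% | 16.5% |
| Mann-Whitney alone | 11.0% | 10.3% |
| Welch alone | 5.2% | 4.8% |
| Two-step, pooled t first | 16.7% | 16.3% |
| Two-step, Welch first | 6.3% | 5.8% |

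If normality is checked on the residuals of both groups together, the two-step rule at 21/63 gives 14.8% (pooled first) or 9.5% (Welch first). Mixing SDs of 9 and 4 makes the combined residuals look non-normal, so Mann-Whitney is used more often.

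**4. Skewed data, where the fallback is actually used.** With shifted lognormal data of shape 0.3 to 0.6 (assumed), equal means and SDs 9 and 4, the two-step rule with Welch first rejects in about 14-27%. Welch alone rejects in about 5.5-7.4%. With gamma data of skewness 0.5 and 1 (also assumed), the two-step rule with Welch first gives 8.5% and 15.5%; Welch alone gives 5.4% and 5.7%.

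**5. Sensitivity to the SDs** (normal data, 21/63). With SDs 6 and 4: pooled t 10.1%, Mann-Whitney 7.4%, Welch 4.8%. With equal SDs all three are near 5%.

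**6. Power at the planned difference** (normal data). Welch 80.7%, Mann-Whitney 86.1%, pooled t 94.0%. The higher figures are not a real gain, because those tests also reject too often when the means are equal.

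**The case against.** A reader might infer that the plan prescribes a pooled t test, so that its principal test runs at 11-17% error. The document does not support this. The analysis section says only t test; the unequal-variance form is named for LGE where it is sized, and the two sections can be read together. On that reading, with a per-group check, the rule gives about 6% on normal data. The range 11-17% spans two single tests and is not the error rate of the written rule. The variant and the normality criterion are also details that an article may leave to a SAP, so silence on them alone would be no finding.

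A second objection is that Mann-Whitney is valid for its own null. If AF status had no relation to LGE, the two distributions would be identical and every test here would hold about 5%. The hypothesis under Objectives says only that LGE is greater in AF patients, without mentioning means. This stands as a limit on the claim: the Mann-Whitney figures are errors against the equal-means null that the sizing text states. Reading the null as equal medians does not bring the rate back to 5%, however: with gamma data of skewness 0.5 to 2 and SDs 9 and 4, Mann-Whitney then rejects in 11-13%.

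Third, the SDs are planning values from pilot data (the pilot figure shows 8 stroke and 8 control patients), and the inflation shrinks if they are closer together.

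What these objections do not remove is the Mann-Whitney switch. It is written into the article, it applies to LGE, and it takes effect when the data are skewed, which is where it departs furthest from the test that was powered.

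**Conclusion.** The point holds for LGE in a conditional form. The sizing uses an unequal-variance t test of equal means, and the analysis rule does not carry that test forward. The consequence depends on how the rule is read:

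- t test pooled, normal data: about 16-17% false positives.
- Mann-Whitney taken alone, normal data: about 10-11%.
- Two-step rule with Welch first and a per-group check, normal data: about 6%.
- Two-step rule with Welch first, skewed data: about 14-27%, against about 5.5-7.4% for Welch alone.

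These figures assume equal means, the plan's SDs of 9 and 4 and a Shapiro-Wilk check; the last line also assumes lognormal shapes of 0.3 to 0.6. The stated 80.8% power is correct for the test named in the sizing.

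It would also be wrong to extend the point to sphericity. That comparison was sized with the same SD in both groups, and with equal SDs all the tests stay near 5%.

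**What to change.** In the Data analysis section, state that LGE burden is compared between AF and non-AF patients by the difference in means with a 95% confidence interval from the unequal-variance (Welch) t test, whatever a normality check shows. State that Mann-Whitney or an analysis on a transformed scale is a sensitivity analysis only.

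On normal data this holds the error near 5% and matches the stated 80.8% power; under the skewed shapes tried it stays at about 5.5-7.4%. Sphericity can keep its equal-variance test, though Welch would do no harm there.

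The cost is one sentence, with no further patients or data. It should be settled before the outcome data are analysed, so that the choice of test cannot follow the results.

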## Objectives

The overall research aim is to produce a substrate-based predictive model using CMR and electrocardiographic parameters that may better identify ESUS patients at risk of developing AF.

The principal research question is to determine if atrial CMR imaging can predict the occurrence of AF in advance of the clinical arrhythmia in patients with confirmed ischemic stroke. The specific hypotheses that will be tested are as follows: (1) left atrial LGE in patients with ESUS is greater in patients with AF than those without AF documented by ILR; and (2) left atrial sphericity in patients with ESUS is greater in those patients with AF than those without AF documented by ILR.

The secondary research question is to determine whether electrocardiographic parameters can predict the occurrence of AF in advance of the clinical arrhythmia in patients with confirmed ischemic stroke. The specific hypotheses that will be tested are as follows: (3) PTFV_1_ in patients with ESUS is greater in those patients with AF than those without AF documented by ILR; and (4) supraventricular ectopy in patients with ESUS is greater in those patients with AF than those without AF documented by ILR.

As described in Data Analysis, below, further analysis will be performed to combine structural and electrical variables into a single score to improve prediction of AF status, which can be employed in future randomized controlled trials.

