For respiratory-navigated imaging, a second LGE sequence is performed 20–25 minutes after gadolinium enhancement. This comprises an ECG-triggered free-breathing diaphragmatic navigated 3D inversion recovery spoiled gradient echo sequence (dNav LGE) that conforms to current clinical standards within our institution for atrial imaging. Coverage includes the left and right atrium. Typical parameters are as follows: TR 4.2 ms, TE 1.8 ms, flip angle 20°, centric k-space ordering, 1.3 × 1.3 × 4 mm^3^ acquired voxel size with interpolation to 1.3 × 1.3 × 2 mm^3^ during image reconstruction, SPIR fat suppression, anterior-posterior phase encoding direction, navigator gating acceptance window of 5 mm in end-expiration.

For all 3 of the 3D sequences (CE-MRA, iNav LGE, dNav LGE) subject-specific trigger delay and acquisition window are identified using the 4-Chamber cine image to identify atrial diastole and reduce cardiac motion artefact. The field of view is identical in both LGEs and the CE-MRA to facilitate registration between the images during postprocessing.

Primary structural metrics collected from CMR imaging include left atrial surface area and volume, visual and quantitative LGE assessment, and sphericity. Secondary anatomical metrics collected include left atrial appendage orifice size and flow.

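### The ordered LGE grades fall, on the natural reading, under a general chi-square test that ignores their order and so does not test whether LGE is greater in AF

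*Protocol article*

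**What the plan says.** Four places in the protocol article bear on this.

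- **Objectives.** Hypothesis 1 is directional: "left atrial LGE in patients with ESUS is greater in patients with AF than those without AF documented by ILR".
- **Cardiac magnetic resonance imaging.** The primary structural metrics to be collected are "left atrial surface area and volume, visual and quantitative LGE assessment, and sphericity".
- **Data analysis, tests.** Normally distributed groups are compared by *t* test; "otherwise, a Mann-Whitney *U* test will be used". The next sentence says that the χ² "test will be used for categorical data". Significance is *P* < .05.
- **Data analysis, grading.** Patients are placed in grades by "combined assessment of both LGE methods as none, mild, moderate, or severe LGE". No test is named in that sentence, and the one after it concerns Kaplan-Meier curves.

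The sample size section powers the quantitative LGE burden, "with a significance level (alpha) of 0.05 using a 2-sided 2-sample unequal-variance *t* test". It gives no power for the visual grades and no expected grade distribution.

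**The concern.** None, mild, moderate and severe form an ordered scale. A general chi-square test on a 2 × 4 table gives the same *P* value however the four columns are arranged. It asks whether the two grade distributions differ in any way, whereas Hypothesis 1 asks whether LGE is greater in AF.

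Two errors of interpretation follow. If AF moves patients up the scale with little change in spread, the test divides its power among three contrasts and can miss a real graded association. If AF mainly widens the distribution, with more patients at both ends, the test can be significant although LGE is no greater on average, and that result could be taken as support for Hypothesis 1.

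**Working it through.** **Inputs from the article (Sample size justification).** 21 AF and 63 non-AF patients; mean LGE burden 47.0 and 41.0; SDs 9.0 and 4.0; two-sided α = 0.05.

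**Assumptions.** The article gives no grade distribution, so several were tried. Grades were generated either from a proportional-odds shift or by cutting a normal LGE burden at three points. Visual grades need not follow the quantitative burden, so the second route is an illustration.

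**Step 1: the article's own figure.** For the unequal-variance *t* test:

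- SE = √(9²/21 + 4²/63) = √(3.857 + 0.254) = 2.028
- noncentrality = 6/2.028 = 2.96
- Satterthwaite df = 22.7
- power from the noncentral *t* = 80.8%

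This matches the stated 80.8%.

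**Step 2: tests compared by simulation (21 v 63, 40,000 runs per scenario).**

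- General chi-square: X² = Σ(O − E)²/E over the 2 × 4 table, df = non-empty columns − 1.
- Trend: scores 0 to 3, 1 df.
- Rank (Mann-Whitney): the same statistic with midranks as scores, which corrects for ties.

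When the two groups have the same grade distribution, all three reject in about 5% of runs.

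**Step 3: upward shift, similar spread.** Proportional odds, with non-AF grades assumed to be 30/35/25/10%:

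| Odds ratio | Chi-square | Trend | Rank |
|---|---|---|---|
| 2 | 23% | 33% | 32% |
| 2.5 | 37% | 52% | 51% |
| 3 | 50% | 67% | 66% |
| 4 | 71% | 85% | 85% |

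Non-AF grades of 30/40/20/10% give the same picture. With 25% in each grade and an odds ratio of 3, chi-square has 47% and trend 65%.

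Normal burden with equal SDs, cut at pooled quartiles: difference 6 and SD 8.3 gives 57% v 75%; difference 4 and SD 5.7 gives 54% v 72%. Over these scenarios chi-square loses 10 to 18 points. The loss is about 7 points where its power is already 90%.

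**Step 4: the article's planning SDs.** With 47 (SD 9) v 41 (SD 4) cut at pooled quartiles, the grade probabilities are 17.6/10.4/14.5/57.5% in AF and 27.5/29.9/28.5/14.2% in non-AF. Power is 93% for chi-square, 84% for trend and 83% for rank. At five other sets of cut-points chi-square has 80 to 99% and trend 70 to 98%, with chi-square higher each time by 1 to 10 points. At SD 7 v 4 the two are level at 95%.

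**Step 5: how much of that is spread.** Keep SDs 9 and 4, set both means to 41, and cut at pooled quartiles. Grade probabilities become 36.2/13.8/13.8/36.2% in AF and 21.3/28.7/28.7/21.3% in non-AF. The average grade is the same in both groups, yet chi-square is significant in 49% of runs, against 8% for trend and for rank. With the AF mean lower than the non-AF mean (39 v 41, same SDs), chi-square is still significant in 58%.

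**The case against.** **The link between test and grades is inferred.** The chi-square sentence is generic, and the grading sentence names no test. The Mann-Whitney sentence could be stretched to cover the grades. This stands as a caution. But that sentence is worded as the fallback for groups that are not normally distributed, and chi-square is the only test named for categorical data. If the sponsor means Mann-Whitney, saying so settles the point.

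**An article may leave such detail to the full plan.** This is fair for a missing test. Here, though, a test is named for this type of data, and it is one that does not suit an ordered scale.

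**Chi-square has more power under the article's own figures.** This stands (step 4). A reader might infer that chi-square simply loses power for the hypothesised effect; the planning SDs do not support that as a general statement. Step 5 shows that part of the advantage is a response to spread, which says nothing about direction.

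**Importance.** A reader might also infer from the word primary that the visual grade is a primary endpoint. The list in question describes which metrics are collected. Hypothesis 1 does not mention visual grades, and the sample size rests on quantitative burden.

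**Small cells.** With 21 AF patients over four grades, an expected count below 5 occurs in more than 95% of simulated tables. It is tempting to call the test invalid, but its type I error stays at about 5%, so this is no ground for change.

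**Conclusion.** The point holds as a minor one. On the natural reading, ordered LGE grades are to be compared by a test that ignores order and therefore does not test Hypothesis 1. The consequence depends on how AF changes the grades:

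- for an upward shift with similar spread, about 10 to 18 points of power are lost over most of the range;
- with spreads as unequal as the planning SDs, chi-square rejects more often than trend, but it also rejects in about half of trials when the means are equal.

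These sizes rest on assumed grade distributions and cut-points and on the planned 21 and 63 patients. The lack of fit with a directional hypothesis does not depend on those assumptions. The powered comparison of quantitative LGE burden and the sample size are unaffected.

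**What to change.** In Data analysis, state that the ordered LGE grades will be compared between AF and non-AF patients by a trend test (for example Cochran-Armitage with scores 0 to 3) or by the Mann-Whitney test already in the plan. Name one of them, and keep the chi-square test for unordered factors.

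The cost is one sentence, with no new data and no change in sample size. There is a small downside: either test is less sensitive to non-monotone patterns or to differences in spread. Under the article's unequal SDs, rejection was up to about 10 points lower with trend, and about 11 points lower with the rank test at one set of cut-points (96% for chi-square v 84%). The study does not hypothesise such patterns; if spread is of interest, the full grade table can be shown alongside.

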### Noninvasive electrophysiological data

All patients will undergo a 12-lead surface ECG and 24 hours of heart rhythm monitoring using telemetry or 24-hour Holter prior to insertion of an ILR (LINQ; Medtronic, Mounds View, MN). Electrocardiographic metrics to be assessed include mean heart rate, atrial high rate episodes, atrial ectopy burden, PTFV_1_, and PR interval.

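### The combined AF score is tuned and chosen in one cohort with about 21 expected AF cases and no stated validation, so an uncorrected AUC for a fitted score would be too high

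*Protocol article*

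**What the plan says.** All references are to the protocol article.

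- **Aim.** Objectives gives a substrate-based predictive model as the overall aim. It describes the combined score as usable in future randomised trials.
- **Method.** Data analysis leaves the way of combining variables open: "the use of logistic regression, shallow classifiers, atrial computational modeling, or combining variables using summated z-scores will be explored to improve the predictive value".
- **Threshold.** Fibrosis assessment plans a ROC analysis over a range of predefined intensity-ratio thresholds, to find the one that best separates AF from non-AF patients for the model. Data analysis adds a ROC search for an LGE cut-off. Sample size justification had used a ratio above 0.97 for the pilot data.
- **Candidate metrics.** Cardiac magnetic resonance imaging: "Primary structural metrics collected from CMR imaging include left atrial surface area and volume, visual and quantitative LGE assessment, and sphericity" (five), plus appendage orifice size and flow as secondary metrics (two). Noninvasive electrophysiological data: "Electrocardiographic metrics to be assessed include mean heart rate, atrial high rate episodes, atrial ectopy burden", PTFV1 and PR interval (five). Objectives names four of these in its hypotheses: LGE, sphericity, PTFV1 and supraventricular ectopy.
- **Cohort.** "We anticipate that our study population will have a 3:1 ratio of non-AF and AF patients". The power statement reads "Group sample sizes of 21 and 63 would achieve 80.8% power to reject the null hypothesis of equal means", and 92 patients are to be recruited to allow for 10% loss.
- **AUC precision.** Sample size justification gives 95% interval widths of 0.21 to 0.28 for AUCs of 0.85 to 0.65, based on the whole cohort.

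**The concern.** Three choices are left to the data: the LGE threshold, the metrics that enter the score, and the method that combines them. The threshold is chosen against AF status, and the methods are explored in order to raise predictive value, all in the same patients. With so few AF cases, a fitted score adapts to chance features of those patients, so its AUC there exceeds its AUC in new patients. The article describes no second cohort and reserves no part of this one.

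The score is meant to carry forward. Trial significance foresees a trial in which atrial substrate guides anticoagulation, and suggests that the model could remove the need for loop recorders. An inflated AUC could make a weak score look ready for that step. The published interval widths would not warn the reader, because they contain no uncertainty from building the model.

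**Working it through.** **1. The plan's own figures.**

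*Power.* Inputs: "This analysis suggested a population mean difference of 6% in left atrial LGE burden between AF and non-AF patients", "with standard deviations of 9.0 for group 1 and 4.0 for group 2", "with a significance level (alpha) of 0.05 using a 2-sided 2-sample unequal-variance" t test, and groups of 21 and 63. The standard error is √(81/21 + 16/63) = √4.111 = 2.03, and the noncentrality is 6/2.03 = 2.96. With 22.7 Welch-Satterthwaite degrees of freedom, power is 80.8%, as stated. The sphericity power of 82.5% also reproduces.

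*AUC widths.* Hanley-McNeil: SE² = [A(1−A) + (n₁−1)(Q₁−A²) + (n₀−1)(Q₂−A²)]/(n₁n₀), where Q₁ = A/(2−A) and Q₂ = 2A²/(1+A). The width is 2 × 1.96 × SE.

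| AF / non-AF | AUC 0.85 | AUC 0.65 |
|---|---|---|
| 21 / 63 | 0.218 | 0.284 |
| 23 / 69 | 0.208 | 0.272 |

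The stated 0.21 and 0.28 agree within 0.01. The formula takes the marker as given before the data are seen.

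**2. Events per candidate.** Expected AF cases: 92 × 0.9 × 0.25 = 20.7, about 21. Candidate metrics: 5 + 2 + 5 = 12. Ratios: 21/12 = 1.75 if all enter, and 21/4 = 5.25 if only the four hypothesised markers do.

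**3. Optimism.** 400 data sets per setting were simulated, each with 21 AF and 63 non-AF patients. Each score was built on the 84 patients, and its AUC there was compared with its AUC in 4,000 new patients. Assumptions not in the article: normal predictors, pairwise correlation 0.3, four equally informative predictors (none in the no-signal row), and best attainable AUC from 0.50 to 0.85. Results for logistic regression:

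| Best attainable AUC | 12 metrics: building / new (gap) | 4 markers: building / new (gap) |
|---|---|---|
| 0.50 (no signal) | 0.747 / 0.500 (0.25) | 0.636 / 0.500 (0.14) |
| 0.65 | 0.780 / 0.575 (0.21) | 0.696 / 0.608 (0.09) |
| 0.75 | 0.840 / 0.679 (0.16) | 0.781 / 0.725 (0.06) |
| 0.85 | 0.904 / 0.790 (0.11) | 0.869 / 0.834 (0.04) |

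Other methods in the same data sets:
- Linear discriminant analysis, standing in for shallow classifiers, behaves like logistic regression.
- Summated z-scores with pre-set signs have a gap of less than 0.01 in every setting.
- Z-scores with signs taken from the data have gaps of 0.09 to 0.16 with 12 metrics, and about 0 to 0.11 with four.
- Taking the best of logistic regression, discriminant analysis and pre-set z-scores adds at most about 0.002 to the logistic gap. These are similar linear scores, so this says little about more flexible classifiers.

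Threshold tuning and atrial computational modelling were not simulated.

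**4. The plan's own effect sizes.** Sphericity: 3.0/3.3 = 0.91 SD. LGE: 6.0/√((81 + 16)/2) = 6.0/6.96 = 0.86 SD. With only these two informative among independent normal predictors, the logistic AUC is 0.83 in the building data against 0.79 in new patients with four predictors (gap 0.04). With 12 it is 0.88 against 0.75 (gap 0.13). At 0.5 SD each, the gaps are 0.07 and 0.19.

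**The case against.** The strongest objection is that much of this is silence. The article says methods will be explored; it does not say that the score's AUC will be reported uncorrected. Bootstrap correction and cross-validation are often left to a full protocol or analysis plan, and neither is shown. The full-cohort precision statement does not exclude them, since resampling also uses every patient. This stands. A reader might infer that the score is assessed only on the data that built it and that its AUC will be badly inflated. The article does not support that inference.

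Three further points stand:
- Twelve is a count of collected metrics, not a stated model list. Two are labelled secondary, and visual and quantitative LGE measure the same thing.
- Bias depends on the method, and pre-set z-scores have almost none. With the planned effects and four markers the gap is only 0.04.
- The article does not tie its interval widths to the combined score, and as figures for a fixed marker they are correct.

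The objection does not dispose of the point. Choosing the threshold against AF status for use in the model, and searching methods to raise predictive value, are stated plans. Calling the score further or exploratory analysis fits poorly with an overall aim of a predictive model and with a score intended for later trials.

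**Conclusion.** The point holds in a conditional form. For a fitted logistic score, an AUC taken from the building data would be too high by about 0.04 to 0.14 with the four hypothesised markers, and by 0.11 to 0.25 with all 12 collected metrics. The larger gaps are comparable to the whole stated interval width. For summated z-scores with pre-set signs the gap is about zero. These sizes rest on the simulation assumptions above and leave out any effect of tuning the threshold or selecting the method.

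The widths of 0.21 to 0.28 are right for a single fixed marker. They should not be carried over to a selected score, or to LGE at a threshold chosen on the outcome. The group comparisons of LGE and sphericity, which answer the principal question, are outside this point.

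**What to change.** 1. Name one primary score on LGE, sphericity, PTFV1 and supraventricular ectopy. A penalised logistic model or z-scores with pre-set signs would both serve; which to use is partly preference.
2. Either fix the LGE threshold at the pilot value (ratio above 0.97), which gives up the planned search for the primary score, or keep the search and repeat it in every resample.
3. Report a bootstrap optimism-corrected AUC and calibration slope, with every selection step repeated inside the resampling.
4. Label the other methods and metrics exploratory, and correct any AUC reported for them in the same way.
5. State that the AUC interval widths in Sample size justification apply to a single prespecified marker.

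If the full protocol or analysis plan already contains these steps, a sentence in Data analysis saying so is enough. No extra patients or measurements are needed, and all analysable patients stay in the analysis. The cost is a little more programming and a lower reported AUC.
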